**5.4.2 The Activation of HIV Reservoir Detection**

a. Plasma HIV RNA at Different Follow-Up Points: Detection and evaluation are based on the quantitative detection kit of human immunodeficiency virus nucleic acid.

b. HIV-1 RNA in cells at 24 Weeks: PBMCs are isolated from peripheral blood. Following cell lysis and intracellular viral RNA extraction, the RNA is reverse-transcribed into cDNA. HIV-1 RNA is detected in PBMCs by RT-PCR.

c. Changes in the function of HIV Gag-specific CD8+T cells.

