**Table 1 ASC22 clinical trial flow chart**

|  | **Screening perioda** | | **Treatment period** | | | | | | **Screening period** | | |
| --- | --- | --- | --- | --- | --- | --- | --- | --- | --- | --- | --- |
| **V1** | **V2** | **V3** | **V4** | **V5** | **V6** | **V7** | **V8** | **V9** | **V10** | **V11** |
| **Screening** | **Baseline** | **Week 2** | **Week 4** | **Week 6** | **Week 8** | **Week 10** | **Week 12** | **Week 16** | **Week 20** | **Week 24** |
| **Visit time** | **Day- 28~Day-2** | **Day 0** | **Day15**  **±2** | **Day 29**  **±2** | **Day 43**  **±2** | **Day 57**  **±2** | **Day 71**  **±2** | **Day 85±2 /Early termination** | **Day 113±5** | **Day 141±5** | **Day 169±2** |
| **Informed consent** | **×** |  |  |  |  |  |  |  |  |  |  |
| **Demographic** | **×** |  |  |  |  |  |  |  |  |  |  |
| **Medical history, treatment history, and history of drug abuse** | **×** |  |  |  |  |  |  |  |  |  |  |
| **Physical examination** | **×** | **×** | **×** | **×** | **×** | **×** | **×** | **×** | **×** | **×** | **×** |
| **Blood pregnancy test**  **(if applicable)** | **×** |  |  | **×** |  | **×** |  | **×** |  |  |  |
| **Height, weight, vital signsb** | **×** | **×** | **×** | **×** | **×** | **×** | **×** | **×** | **×** | **×** | **×** |
| **Blood routined** | **×** | **×a** | **×** | **×** | **×** | **×** | **×** | **×** | **×** | **×** | **×** |
| **Blood biochemistry**  **(including myocardial enzymes)e** | **×** | **×a** | **×** | **×** | **×** | **×** | **×** | **×** | **×** | **×** | **×** |
| **Urine routinef** | **×** | **×a** | **×** | **×** | **×** | **×** | **×** | **×** | **×** | **×** | **×** |
| **Coagulation functiong** | **×** | **×a** | **×** | **×** | **×** | **×** | **×** | **×** | **×** | **×** | **×** |
| **Thyroid functionh** | **×** | **×a** |  | **×** |  | **×** |  | **×** |  |  | **×** |
| **Adrenalinei** | **×** | **×a** |  | **×** |  | **×** |  | **×** |  |  |  |
| **Blood sugarj** | **×** | **×a** |  | **×** |  | **×** |  | **×** |  |  |  |
| **Twelve-lead electrocardiogramc** | **×** | **×** | **×** | **×** | **×** | **×** | **×** | **×** |  |  |  |
| **Chest CT scan** | **×** |  |  |  | **×** |  |  | **×** |  |  |  |
| **Cardiac ultrasound** | **×** |  |  |  | **×** |  |  | **×** |  |  |  |
| **Abdominal ultrasonography (B ultrasound)** | **×** |  |  |  | **×** |  |  | **×** |  |  |  |
| **Plasma HIV Viral load (HIV-1 RNA)** | **×** | |  | **×** |  | **×** |  | **×** |  |  |  |

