| **T cell immunek** | **×** | |  | **×** |  | **×** |  | **×** |  |  |  |
| **HIV Gag-specific CD8+T** | **×** | |  | **×** |  | **×** |  | **×** |  |  |  |
| **HIV reservoir**  **(HIV-1 DNA)** | **×** | |  | **×** |  | **×** |  | **×** |  |  |  |
| **ASC22 administration** |  | **×** |  | **×** |  | **×** |  |  |  |  |  |
| **Chidamide dispensing drug** |  | **×** | **×** | **×** | **×** | **×** | **×** |  |  |  |  |
| **Distribute medication diary cards** |  | **×** | **×** | **×** | **×** | **×** | **×** |  |  |  |  |
| **Recycling medication diary cards** |  | **×** | **×** | **×** | **×** | **×** | **×** | **×** |  |  |  |
| **AES** | **×** | | | | | | | | **×** | **×** | **×** |
| **Combination therapy** | **×** | | | | | | | | **×** | **×** | **×** |
| **Summary and analysis of test completion status** |  |  |  |  |  |  |  |  | **×** | | |

a. When the screening test and the day of drug administration coincide, relevant laboratory tests can be shared. Typically, results of pertinent safety tests conducted within approximately one week from the date of signing the informed consent form to the day of drug administration are acceptable.

b. Height measurement is only conducted during the screening period. Vital signs include body temperature, heart rate, respiration rate, and blood pressure.

c. ECG should be performed before ASC22 administration (within ±30 minutes) on the day of drug administration.

d. Blood routine tests include total WBC, WBC differential count (neutrophil [N] absolute count, lymphocyte [L] count, monocyte [M] count, eosinophils [E] count, absolute basophil [B] count), total RBC, HB, PLT, and HCT.

e. Blood biochemistry tests include total protein, albumin, total cholesterol, LDL, HDL, triglycerides, urea nitrogen/urea, uric acid, creatinine, alkaline phosphatase, lactate dehydrogenase, total bilirubin, direct bilirubin, indirect bilirubin, AST, ALT, calcium, phosphorus, magnesium, potassium, sodium, chloride, and serum amylase. Cardiac enzyme spectrum examination includes troponin-I, CK, and CK-MB.

f. Urine routine includes specific gravity, pH, urine sugar, protein, casts, ketone bodies, blood cells, and RBC.

g. Coagulation function includes PT, APTT, INR, FIB, TT, and D-dimer.

h. Thyroid function includes TSH, FT3, FT4, T3, T4. No relevant drug interference exists, and the test results within two weeks of the screening or baseline period are acceptable.

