**5.2 Test Process**

This project is a prospective, single-center, single-arm clinical trial study. The plan is to enroll 15 PLWH. Following informed consent, each subject will receive a single dose of 1 mg/kg intravenous ASC22 on the first day, followed by a subcutaneous injection of ASC22 (drawing an appropriate volume of ASC22 according to the participant's needs and then injecting subcutaneously, with the injection speed not exceeding 0.06 ml/s). Additionally, oral chidamide intervention will be administered twice a week simultaneously, with a dosage of 10 mg.

Throughout this period, the ART treatment will be continued. The treatment period will last 12 weeks, and follow-up will extend until 24 weeks. Peripheral blood samples will be collected before the ASC22 intervention(every four weeks). Approximately 20 ml of blood will be collected during each session, and subjects will undergo medical evaluation concurrently.

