**5.4.3 The changes of HIV reservoir**

Digital droplet PCR is used to detect HIV-1 DNA in cells at various visit points (copies/106 PBMCs). PBMCs are isolated from 10ml whole blood samples. The QX100 digital droplets PCR system (Bio-Rad) is utilized to quantify the amount of HIV-1 DNA per 106 PBMCs.

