**6 Efficacy and safety outcomes**

The primary outcomes were assessed by quantifying changes in CA HIV RNA, total HIV DNA, integrated HIV DNA in PBMCs, and plasma HIV RNA, as well as by analyzing variations in the functionality of HIV Gag- and Pol- specific CD8+ T cells from baseline to post-treatments. In addition, changes in CD4+ T cell counts, CD8+ T cell counts, and CD4/CD8 ratios were monitored at baseline and at different time points during treatment.

Safety Outcomes: number of participants experienced with drug-related AEs of Grade 3 or Higher.

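### CA HIV RNA is a primary change-from-baseline outcome, but the text times its assay only at Week 24 and Table 1 has no row for it, so the written schedule yields no baseline/post-treatment pair

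*Protocol*

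**What the plan says.** **Outcome.** Section 6, repeated in the Program summary, states: "The primary outcomes were assessed by quantifying changes in CA HIV RNA, total HIV DNA, integrated HIV DNA in PBMCs, and plasma HIV RNA". The same sentence adds the "functionality of HIV Gag- and Pol- specific CD8+ T cells from baseline to post-treatments", which fixes the contrast as baseline against post-treatment. CD4+ count, CD8+ count and CD4/CD8 ratio follow in the same paragraph.

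**Assays.** Section 5.4.2(b) gives CA HIV RNA one time: "HIV-1 RNA in cells at 24 Weeks: PBMCs are isolated from peripheral blood". Item (a) of that section has plasma HIV RNA measured repeatedly over follow-up. Item (c) reads "Changes in the function of HIV Gag-specific CD8+T cells" and does not mention Pol. Section 5.4.3 reads "Digital droplet PCR is used to detect HIV-1 DNA in cells at various visit points" and does not say whether total or integrated DNA is meant.

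**Schedule.** Table 1 has rows for plasma HIV RNA, T-cell counts, "HIV Gag-specific CD8+T" and HIV-1 DNA. Each is marked once across screening and baseline and again at Weeks 4, 8 and 12. All are blank at Weeks 16, 20 and 24. There is no CA HIV RNA row.

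**Blood.** Section 5.2 has about 20 ml drawn at four-week intervals ahead of ASC22, without listing assays. Section 5.4.3 isolates PBMCs for HIV-1 DNA from 10 ml.

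**The concern.** A change from baseline needs a baseline value and a later value from the same participant. For CA HIV RNA the protocol states a single time, and it is not baseline. The stated time also falls at a visit where Table 1 schedules safety assessments but no virology, reservoir or T-cell sample. A site that follows section 5.4.2(b) and Table 1 to the letter would have nothing to subtract, and no sample on which to run even the Week 24 assay.

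The timing matters for interpretation too. CA HIV RNA is listed under reservoir activation, and the title describes a shock-and-kill strategy. Activation by the study drugs would be looked for while they are being given, not months after they stop.

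This is not something to leave to a statistical analysis plan. The protocol decides which samples are taken and when, and no analysis method can supply a baseline that was never assayed.

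**Working it through.** The plan gives no figure on this point to reproduce. The check sets each virological or T-cell-function component of the primary outcome against the times stated in Table 1 and sections 5.4.2 to 5.4.3.

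| Primary component (section 6) | Named in assay text | Times stated | Baseline | Post-baseline | Pair? |
|---|---|---|---|---|---|
| Plasma HIV RNA | 5.4.2(a) | Screening/baseline, Weeks 4, 8, 12 | yes | 3 | yes |
| Total HIV DNA | not by name (5.4.3: HIV-1 DNA) | Screening/baseline, Weeks 4, 8, 12 if the generic row covers it | yes, if covered | 3, if covered | yes, if covered |
| Integrated HIV DNA | not by name (5.4.3: HIV-1 DNA) | as for total | yes, if covered | 3, if covered | yes, if covered |
| Gag-specific CD8+ function | 5.4.2(c) | Screening/baseline, Weeks 4, 8, 12 | yes | 3 | yes |
| Pol-specific CD8+ function | no | none by name | none by name | none by name | not by name |
| CA HIV RNA | 5.4.2(b) | Week 24 | no | 1 | **no** |

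**Distance of the one stated time from treatment.**

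- Table 1 gives ASC22 at Day 0, Week 4 and Week 8. From the last dose to Week 24: 24 − 8 = 16 weeks.
- Section 5.2 sets a 12-week treatment period. From its end to Week 24: 24 − 12 = 12 weeks.
- Section 3.1.1 gives a mean ASC22 elimination half-life of about 8.3 days. 16 × 7 = 112 days, and 112 / 8.3 = 13.5 half-lives since the last dose.

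**Could section 5.2 supply the Week 24 sample?** Its draws are tied to ASC22 administration, which in Table 1 ends at Week 8. It does not provide a research sample at Week 24.

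**Could existing samples support the outcome?** Table 1 already requires PBMC-based HIV-1 DNA at screening/baseline and Weeks 4, 8 and 12. At the draws described in section 5.2, about 20 − 10 = 10 ml remains after the HIV-1 DNA volume. The protocol does not say how that remainder is divided among the other assays.

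**The case against.** The strongest reply is that this is an undocumented time point, not a missing outcome. Section 6 itself presupposes a baseline value, PBMCs are collected at baseline and three later visits, and section 5.4.2(b) does not say that Week 24 is the only time. In translated text, the phrase could mean over the 24 weeks of the study.

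Part of this stands. A reader might infer that the change in CA HIV RNA cannot be estimated at all; the documents do not support that, because suitable cells are already being drawn. The over-24-weeks reading is weak, however. Section 5.4.2(a) and section 5.4.3 use plainly different wording for repeated measurement, and that reading would still leave Table 1 without a CA HIV RNA row and without virology after Week 12.

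Other stronger inferences also fail:

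- **That the trial cannot say anything about activation.** Plasma HIV RNA is listed under the same heading and has a baseline and three later values, at Weeks 4, 8 and 12.
- **That integrated HIV DNA is never scheduled.** The HIV-1 DNA row names neither form. If it excludes integrated DNA for that reason, it excludes total DNA as well. What holds is that nothing tells the two apart.
- **That half the primary outcomes lack data.** Only CA HIV RNA has a stated time that rules out a pair. Pol and integrated DNA are naming gaps in assays otherwise scheduled. The CD4+ and CD8+ counts, from which the ratio follows, sit in the same outcome paragraph and are scheduled.
- **That missing Week 24 virology defeats a durability aim.** The protocol states no such aim, so adding plasma RNA, DNA and T-cell marks at Week 24 would be a preference.

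**Conclusion.** The protocol is wrong as written on CA HIV RNA. Section 6, section 5.4.2(b) and Table 1 cannot all be followed and still yield the primary outcome. Followed literally, they give 0 baseline/post-treatment pairs for any of the 15 planned participants, and the single stated time lies 12 weeks after treatment and 16 weeks after the last scheduled ASC22 dose. CA HIV RNA, though not plasma HIV RNA, would then be silent on activation during treatment.

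The Pol and integrated DNA points are lesser: primary outcomes whose names do not appear in the assay sections or Table 1, to be reconciled alongside.

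The conclusion rests on the text and Table 1. Figure 2, the study flow chart, is not shown and might carry further times. It also assumes that the single mark spanning screening and baseline in Table 1 denotes a pre-dose sample. The contradiction is certain on the text at hand; whether baseline CA HIV RNA would be missed in practice is not.

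**What to change.** 1. Amend section 5.4.2(b) and add a CA HIV RNA row to Table 1 at baseline (stated as pre-dose) and Weeks 4, 8 and 12, using the PBMC samples already drawn for HIV-1 DNA.
2. For Week 24, either add a PBMC sample to Table 1 or delete the reference from section 5.4.2(b).
3. Name Pol in section 5.4.2(c) and Table 1, and say in section 5.4.3 and Table 1 which HIV-1 DNA measurement is total and which is integrated. Otherwise remove Pol and integrated DNA from the primary outcomes in section 6 and the Program summary.

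The cost is a protocol amendment and extra assays on blood already collected, plus one tube at an existing visit if Week 24 is kept. Before the amendment is final, the laboratory should confirm that the roughly 20 ml per session covers all the assays, since the protocol allocates only the 10 ml for HIV-1 DNA.

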**5.4.3 The changes of HIV reservoir**

Digital droplet PCR is used to detect HIV-1 DNA in cells at various visit points (copies/106 PBMCs). PBMCs are isolated from 10ml whole blood samples. The QX100 digital droplets PCR system (Bio-Rad) is utilized to quantify the amount of HIV-1 DNA per 106 PBMCs.

**5.4.4 Immunological Examination**

CD4+T cell count, CD8+T cell count, CD4+/CD8+ ratio

**5.4.5 Laboratory Examination and Organ Function Evaluation**

During the comprehensive assessment and clinical observation of subjects' relevant laboratory test indicators and organ functions based on the follow-up time, the following abnormal indicators will be focused on at the specified intervals:

(1) Vital Sign Monitoring: During each follow-up visit, BMI index, body temperature, blood pressure, heart rate, etc., will be checked to assess the occurrence of abnormalities.

(2) Cardiac Function Test: During each follow-up visit, electrocardiogram, myocardial enzyme spectrum, etc., will be examined. Cardiac ultrasound examinations will be conducted during the screening period, after using the experimental drug at week six, and upon completion of the treatment.

(3) Liver and Kidney Examination: During each follow-up visit, blood biochemistry, including liver and kidney function, will be examined. Abdominal B-ultrasound will be conducted during the screening period, after using the experimental drug at week six, and upon completion of the treatment.

(4) Respiratory System Examination: Chest CT examinations will be performed during the screening period, after using the experimental drug at week six, and upon completion of the treatment.

(5) Other Relevant Examinations: At each follow-up, blood routine, urine routine, coagulation function, electrolytes, etc., will be checked accordingly.

Researchers need to comprehensively evaluate the examination above results of the subjects based on the relevant physical reviews conducted at each follow-up visit. If abnormalities are detected in the appropriate tests during the study, timely adjustments should be made based on the clinical situation.

**6 Efficacy and safety outcomes**

The primary outcomes were assessed by quantifying changes in CA HIV RNA, total HIV DNA, integrated HIV DNA in PBMCs, and plasma HIV RNA, as well as by analyzing variations in the functionality of HIV Gag- and Pol- specific CD8+ T cells from baseline to post-treatments. In addition, changes in CD4+ T cell counts, CD8+ T cell counts, and CD4/CD8 ratios were monitored at baseline and at different time points during treatment.

Safety Outcomes: number of participants experienced with drug-related AEs of Grade 3 or Higher.

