**Program summary**

| Basic information | Protocol Number: V20220703  Version/Date: V1.3/20220703  Study drug: Recombinant humanized PD-L1 single domain antibody Fc fusion protein injection  Drug code: ASC22 (previously used code KN035, Envafolimab)  Drug specifications: 1 ml: 200 mg (1 ml/ampoule)  Drug production unit: Alphamab Oncology, jiangsu, China |
| --- | --- |
| Title | Anti-PD-L1 antibody ASC22 in combination with chidamide as a “shock and kill” strategy for HIV functional cure: a phase Ⅱ study |
| Study purposes | Assessing whether ASC22 in combination with chidamide can reduce HIV reservoirs in PLWH with virologically suppressed |
| Study design | Single center, prospective, single-arm, phase Ⅱ study |
| Population | PLWH |
| Sample size | This study estimates that 12 participants will complete the trial, and the dropout rate will be controlled within 15%, so 15 participants are planned to be enrolled. |
| Study treatment | Participants received a subcutaneous injection of ASC22 (1mg/kg) once every 4 weeks for a total of 3 times. Chidamide (10 mg) was administered orally twice weekly for 12 weeks, while continue ART |
| Inclusion criteria | (1) Individuals diagnosed with HIV infection;  (2) Age ≥ 18 years old;  (3) BMI ≥ 18.0 to < 35.0 kg/m2;  (4) Capable and willing to comply with the time requirements for study visits and assessments;  (5) Currently receiving ART for at least 24 months, with two consecutive plasma HIV-1 RNA levels <50 copies/ml, separated by an interval of at least 12 months;  (6) During the screening period, CD4+ T cell count is ≥ 250 cells/µl (including the boundary value), and CD4/CD8 ratio is < 0.9;  (7) Agree to use contraception during participation in the project and for up to 6 months after the end of the trial;  (8) Willing to provide informed consent. |

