| Primary outcomes | The primary outcomes were assessed by quantifying changes in cell-associated (CA) HIV RNA, total HIV DNA, integrated HIV DNA in PBMCs, and plasma HIV RNA, as well as by analyzing variations in the functionality of HIV Gag- and Pol- specific CD8+ T cells from baseline to post-treatments. In addition, changes in CD4+ T cell counts, CD8+ T cell counts, and CD4/CD8 ratios were monitored at baseline and at different time points during treatment. |
| Secondary endpoints | The related symptoms and laboratory tests need to be monitored. These symptoms may include vomiting, fatigue, rash, itching, diarrhea, constipation, borborygmi, fever/chills, headache, palpitations, heat sensation, changes in appetite, gastrointestinal pain, gastroesophageal reflux, touch sensitivity, taste and smell disturbances, dizziness, muscle or joint pain, blisters, oral lesions, conjunctivitis, facial edema, and more.  The laboratory tests include blood routine, liver and kidney function, urine routine, myocardial enzymes, blood sugar, blood coagulation, electrolytes, electrocardiogram, chest CT examination, cardiac ultrasound examination, and abdominal B-ultrasound for liver and kidney examination.  The severity of AEs will be graded according to the CTCAE version 6.0. AEs are defined as any adverse medical events occurring in patients or clinical research participants taking a drug product, regardless of causality with the treatment. The investigator will assess the relationship of each event to the study drug as either reasonably likely or not reasonably likely. AEs are divided into grades 1-5, with grade 3 being serious but not life-threatening and requiring hospitalization, grade 4 being life-threatening and requiring hospitalization, and grade 5 indicating an AE-related death requiring immediate intervention. |
| Statistical Analysis | Statistical analyses were carried out using GraphPad Prism 8.0 (San Diego, CA, USA) and SPSS 15.0 statistical software (Chicago, IL, USA). P-value (P) below 0.05 was considered statistically significant. |

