**2 Study Purpose**

Assessing whether ASC22 in combination with chidamide can reduce HIV reservoirs in PLWH with virologically suppressed

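### At least six unranked primary outcomes, with no lead outcome, time point or direction, stand against a purpose that asks only whether the HIV reservoir falls

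*Protocol*

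**What the plan says.** Section 2 gives the purpose as one question: "Assessing whether ASC22 in combination with chidamide can reduce HIV reservoirs in PLWH with virologically suppressed".

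Section 6 answers it with a list. Its virological part reads: "The primary outcomes were assessed by quantifying changes in CA HIV RNA, total HIV DNA, integrated HIV DNA in PBMCs, and plasma HIV RNA". The same sentence then puts T-cell function on an equal footing with those four markers: "as well as by analyzing variations in the functionality of HIV Gag- and Pol- specific CD8+ T cells from baseline to post-treatments". The Program summary repeats both parts in its row for primary outcomes. In both places a separate sentence brings in the T-cell counts: "changes in CD4+ T cell counts, CD8+ T cell counts, and CD4/CD8 ratios were monitored at baseline and at different time points".

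The only decision criterion is in the Program summary: "P-value (P) below 0.05 was considered statistically significant". The protocol does not rank the outcomes, say how they combine, name a primary visit, or state whether a rise or a fall is wanted.

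The measurement sections do separate the markers. Section 5.4.2, headed "The Activation of HIV Reservoir Detection", covers plasma HIV RNA, HIV-1 RNA in cells and Gag-specific CD8+ function. Section 5.4.3, on reservoir changes, covers only HIV-1 DNA by droplet digital PCR.

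**The concern.** Choosing the primary outcome is a protocol decision. Here the protocol has made it in a way that leaves the trial's question without a defined answer.

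There are two consequences. First, with several co-equal primary outcomes and one generic threshold, the chance that at least one is significant when nothing has happened is well above 5%. The design is single-arm, so no control group would help to expose a chance change.

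Second, the outcomes do not point the same way. The title calls this a "shock and kill" strategy, and Sections 5.4.2 and 5.4.3 divide the markers accordingly: RNA reflects activation, DNA reflects the reservoir. Entry requires plasma HIV-1 RNA below 50 copies/ml, so the movement readily visible in that marker is upward. Section 6 nevertheless pools all of them as undirected changes. A significant rise in cell-associated or plasma RNA with flat HIV DNA could be reported as a primary result, although Section 2 asks about a smaller reservoir.

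**Working it through.** **Inputs**
- Threshold: 0.05 (Program summary). Sidedness is not stated; two-sided is assumed.
- Completers: n = 12 (Section 5.1).
- Number of outcomes: six from Section 6 (four virological, two CD8+ function). Adding CD4, CD8 and CD4/CD8 gives an upper count of nine.
- Correlation between outcomes: not given. It is assumed, with a range of 0 to 0.8.

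**The plan's own figure.** The only computable design number is enrolment: 12/(1 − 0.15) = 14.1, rounded up to 15. This agrees with Section 5.1. The protocol states no power and no family-wise error rate, so there is nothing else to reproduce.

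**One test per outcome, no true effect.** Under independence, P(at least one P < 0.05) = 1 − 0.95^k.
- k = 6: 1 − 0.7351 = 26.5%
- k = 9: 1 − 0.6302 = 37.0%

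These are roughly 5 and 7 times the nominal 5%.

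The correlated case was simulated with paired t-tests on change from baseline, n = 12, 40,000 replicates and equal correlation between outcomes:

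| Correlation | Six outcomes | Nine outcomes |
|---|---|---|
| 0.3 | 24% | 33% |
| 0.5 | 22% | 28% |
| 0.8 | 15% | 18% |

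**More than one visit.** Table 1 schedules plasma HIV RNA, HIV-1 DNA and Gag-specific CD8+ at Weeks 4, 8 and 12. Section 5.4.2 places HIV-1 RNA in cells at 24 weeks. Table 1 has no separate row for cell-associated RNA, integrated DNA or Pol-specific CD8+. The tests of the six that these sections expressly support are therefore 3 × 3 + 1 = 10, and 1 − 0.95^10 = 40.1% if independent. Positive correlation between visits and markers would lower this.

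**Direction.** A two-sided test at 0.05 puts 2.5% in each tail. With no effect, half of the false positives for any marker would lie in the direction opposite to the one hoped for.

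**One primary outcome compared with splitting the threshold.** For a paired t-test with n = 12 and 80% power, the detectable mean change is 0.89 SD at two-sided 0.05. Bonferroni over six (0.05/6 = 0.0083 each) would need 1.20 SD. With so few participants, naming one outcome costs much less than sharing the error over six.

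**The case against.** The strongest reply is that much of this belongs to a statistical analysis plan that is not shown. Multiplicity adjustment, sidedness and order of testing are commonly fixed there, so their absence here is no finding. That stands. It does not reach the core point: which of six primary outcomes answers Section 2, and whether a rise or a fall is success, should not be left to an analysis plan.

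Several stronger readings are tempting, and the protocol does not support them:
- **A false positive is more likely than not.** One test per outcome gives 26% to 37% at most. Figures of 60% (6 × 3 tests) or 75% (9 × 3) assume every outcome is tested at Weeks 4, 8 and 12. Table 1 does not expressly schedule that for cell-associated RNA, integrated DNA or Pol-specific CD8+.
- **There are nine primary outcomes.** The T-cell counts share the summary's primary row but are described only as monitored. Nine is an upper count.
- **Any one significant change makes the trial positive.** The protocol gives a generic threshold. It does not say that one significant outcome suffices.
- **The protocol prescribes opposite directions.** It states none. The directions are inferred from the title and the two section headings, and the activation heading also covers CD8+ function, so the headings are imperfect evidence. In this kind of strategy, RNA up and DNA down are successive steps of one mechanism. Differing directions are no fault in themselves; leaving success undefined is.

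This is also a small phase II study. That tempers how its P-values should be read, but it does not remove the need for a primary outcome that matches the purpose.

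**Conclusion.** The point holds in this form. The protocol fixes at least six unranked primary outcomes, with no lead outcome, time point or direction, against a purpose that concerns only reservoir reduction. No pattern of results is defined as success or failure.

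The false-positive figures (26% to 37% under independence, 24% to 33% at correlation 0.3, about 40% for the ten expressly supported tests if independent) rest on three assumptions: two-sided tests, no true effect, and no adjustment added elsewhere. An analysis plan could bring the error rate down. It would not by itself settle which marker answers Section 2. That part of the point needs no simulation and does not depend on the assumed correlation.

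**What to change.** Name one primary outcome matched to Section 2: the change from baseline to Week 12 in log10 HIV-1 DNA per 10^6 PBMCs, by the droplet digital PCR assay in Section 5.4.3, tested at two-sided 0.05, with success defined as a reduction.

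Two details must be written in. Section 5.4.3 and Table 1 say only HIV-1 DNA, so state that this is total HIV DNA. The Table 1 mark for this assay spans screening and baseline, so state which pre-dose sample is the baseline.

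Make cell-associated and plasma HIV RNA secondary activation measures. Report integrated HIV DNA, CD8+ function and the T-cell counts as secondary or exploratory, with estimates and 95% confidence intervals.

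Cost: the assay and the Week 12 visit are already scheduled, so no participant, visit or test is added. The other markers lose the primary label, and the change needs a protocol amendment, which Section 10.1 sends to the ethics committee. Choosing total over integrated DNA is a scientific decision for the investigators; what matters is that one is named in advance.
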